#### Interventions

##### Part one

All clinician participants will be given access to the Lung Foundation Australia Pulmonary Rehabilitation Online Training Program (https://lungfoundation.com.au/events/pulmonary-rehabilitation-online-training/). This is a 6-8 hour self-directed online training programme that increases the knowledge and skills of health professionals to deliver evidence-based PR. It has not been developed for specific professions so the same programme will be completed by physiotherapists and AEPs. Modules included are: Establishing a PR programme; The respiratory system and COPD; Comprehensive patient assessment; Spirometry; Assessing exercise capacity; Assessing quality of life; Exercise training; Patient education; Program evaluation and troubleshooting.

After completion of the online training, participants will attend a practical in-person module. The practical module will be a group session, delivered by experts in PR. The practical module will include performing field tests for measurement of exercise capacity and developing exercise prescriptions. Participants will be required to pass a predefined competency threshold. The minimum threshold for the knowledge questionnaire will be 80% of questions correct. The minimum threshold for the practical skills assessment will be achieving a rating of ‘proficient’ in three of the four components for each exercise capacity test and being proficient in the core competencies of each test.

##### Part two

Patient participants allocated to the intervention group will undertake twice weekly PR at their allocated PP for 8 weeks. PP PR programmes will have a maximum of eight participants in any session. PR sessions will follow the Australian and New Zealand PR guidelines (Alison *et al.*, 2017) and consist of at a minimum 30 minutes of lower limb endurance training (e.g., treadmill walking, ground walking, and stationary cycling), strength training and a home exercise programme. As per the training clinician participants received in Part One of the study, participants with CRD will be prescribed an exercise programme from their baseline exercise capacity assessment or a symptom-based prescription from the Borg scale for rating breathlessness or fatigue in accordance with the current evidence-based practice guidelines (Alison *et al.*, 2017). The specific exercises prescribed for each participant will be left to the discretion of the physiotherapist or AEP and will take into account available exercise equipment at their practice, participant goals, and past medical history. Clinicians will document the mode, duration, intensity, type, and progression for each exercise prescribed. A home exercise programme will also be prescribed for each participant. Intervention session logs and home exercise programme logs will be completed to document what was achieved by each participant compared to what was prescribed. This will be used to measure intervention fidelity and adherence. A sample intervention session is outlined in Table 2.

**Table 2. tbl2:** Sample intervention session

Training type	Mode	Intensity	Type	Duration
Lower limb endurance (must include walking)	Walking	80% average speed on 6MWT or 75% peak speed of modified ISWT, aiming for dyspnoea or leg fatigue 3-4 (moderate to somewhat severe) on 0–10 category ratio scale (Zakrisson *et al.,* 2011)	Continuous or interval	Total 30 minutes
	Treadmill	80% average speed on 6MWT OR 75% peak speed of modified ISWT aiming for dyspnoea or leg fatigue 3–4 (moderate-somewhat severe) on 0–10 category ratio scale (Zakrisson *et al.,* 2011) . Start at speed 0.5-1km/hr lower than calculated until familiar with treadmill	Continuous or interval	
	Stationary cycle (if available)	60% peak work rate estimated from 6MWT or dyspnoea or leg fatigue of 3-4 (moderate-somewhat severe) on 0–10 category ratio scale (Zakrisson *et al.,* 2011).	Continuous or interval	
Upper and lower limb strengthening	Resistance bands or dumbbells	3 sets 8–10 repetitions for each exercise at a weight or resistance where these repetitions can just be completed		10–15 minutes
Upper limb endurance	Resistance bands or dumbbells	1-2 sets of 15–20 repetitions for each exercise, at a weight of resistance that causes muscle ‘fatigue’. Low weight, high repetitions		10 minutes

Abbreviations: 6MWT, 6-minute walk test; ISWT, incremental shuttle walk test.

The control group will receive usual care from their GP. At study completion, all participants will be offered the opportunity to return to the centre-based PR waitlist from which they were recruited.

#### Outcomes

Outcome measures for Part One and Two of the study are outlined in Table 3.

**Table 3. tbl3:** Study outcome measures

Part One	Part Two
**Primary outcome**	
Change in participant knowledge as measured by knowledge questionnaire and change in participant self-rated confidence, knowledge, and skills questionnaire before and after training course.	Adherence to the intervention, measured by the proportion of randomized participants who complete the intervention. Defined as at least 12 of the possible 16 sessions (75%).
**Secondary outcomes**	
The proportion of participants meeting proficiency threshold in practical skills assessment.	The proportion of eligible participants randomized (feasibility).
Change in participant self-rated confidence, knowledge, and skills questionnaire at 3 months post training.	The proportion of PR sessions where physiotherapists or AEPs provide exercise prescriptions of appropriate intensity and duration (fidelity).
Maintenance of participant knowledge at 3-months post training course.	Change in exercise capacity (6-minute walk test or incremental shuttle walk test, 1-minute sit-to-stand test) prior to and after 8-week PP PR intervention or 8-week control period.
The proportion of participants meeting proficiency threshold in the knowledge questionnaire before, after training and at 3-months post training.	Change in HRQoL (St George’s Respiratory Questionnaire) prior to and after 8-week PP PR intervention or 8-week control period.
Change in participant self-rated confidence, knowledge, and skills questionnaire at 3-months post training.	Change in Health status (COPD Assessment Test) prior to and after 8-week PP PR intervention or 8-week control period.
Proportion of participants who go on to deliver the intervention.	Number of adverse events.

Abbreviations: PP, private practice; PR, pulmonary rehabilitation; AEP, accredited exercise physiologist; HRQoL, health-related quality of life; COPD, chronic obstructive pulmonary disease.

##### Part one

The primary outcome is change in participant knowledge as measured by knowledge questionnaire and change in participant self-rated confidence, knowledge, and skills questionnaire before and after training course. The knowledge questionnaire is an 11-item multiple choice questionnaire based on a case vignette constructively aligned to the content of the training. The questionnaire can be found in supplemental file 1. The self-rated confidence, knowledge, and skills questionnaire is a 21-item questionnaire consisting of 5-point Likert Scales.

Secondary outcomes include: the proportion of participants meeting proficiency threshold in practical skills assessment; maintenance of participant knowledge 3 months post training course; the proportion of participants meeting proficiency threshold in the knowledge questionnaire before, after training, and 3 months post training; change in participant self-rated confidence, knowledge, and skills questionnaire at 3 months post training, proportion of participants who go on to deliver the intervention.

### Part two

The primary outcome is adherence to the intervention, measured by the proportion of randomized participants who complete the intervention. Completion will be defined as attending 12 of the 16 (75%) allocated sessions (Williams *et al.*, 2014). Secondary outcomes include: feasibility – the proportion of eligible participants randomized; fidelity – the proportion of PR sessions where physiotherapists or AEPs provide exercise prescriptions of appropriate intensity and duration. The proportion of missing data will also be analysed.

Clinical outcome measures will test effectiveness. Dyspnoea will be assessed by the mMRC Dyspnoea Scale (Mahler and Wells, 1988). Exercise capacity will be measured by a field walking test and the 1-minute sit-to-stand. The field walking test performed will be the 6-minute walk test (6MWT) if there is a 30m walking track for the test to be performed according to the European Respiratory Society/American Thoracic Society (ERS/ATS) technical standards (Holland *et al.*, 2014). If there is not adequate space, the incremental shuttle walk test (ISWT) will be performed, again according to ERS/ATS technical standards. The same test will be performed throughout the study for each study participant. Both the 6MWT and ISWT have demonstrated reliability and validity and are responsive to PR (Singh *et al.*, 2014). HRQoL will be measured by the St George’s Respiratory Questionnaire (Jones *et al.*, 1991). Health status will be measured by the COPD Assessment Test (Jones *et al.*, 2009). Both questionnaires have excellent reliability and validity and are responsive to PR (Singh *et al.*, 2001, Kon *et al.*, 2013). Perception of change post intervention will be measured by a 5-point Global Rating of Change Questionnaire.

Number of adverse events will be recorded as a safety outcome measure. Adverse events will be defined as any untoward medical occurrence experienced by a study participant and that does not necessarily have a causal relationship with this treatment. Exacerbations of the participant’s CRD will not be classed as adverse events as they are an expected events due to the nature of the disease but will be recorded and reported as a separate outcome. Qualitative outcome measures will include patient participant experience of participating in the trial, clinician participant experience of participating in the trial, and barriers and facilitators to trial participation and completion.

#### Study procedures

Data for Part One of the study will be collected online by REDCap using surveys. Questionnaires used in Part One have been designed specifically for the study. Data for Part Two will be collected in person. Any participant who desaturates to SpO_2_ <80% on the field walking test will be withdrawn from the study prior to randomization.

Semi-structured interviews will be conducted with a purposeful sample in both clinician and patient participants. The interviews will explore qualitative aspects of the feasibility of the outcome measures and participant’s experience in the study. Clinician interview guides will also explore participant’s experience of upskilling in PR delivery, identifying any barriers or facilitators, and any improvements that could be made. Topic guides will also include exploration of business models and whether clinicians view the intervention as feasible from a business perspective. After the first 2 to 3 interviews, interview guides will be revised if necessary.

The interviews will take place after the completion of Part Two of the study (or earlier if there is attrition). A purposive sampling of patient participants will be taken to capture those who complete or do not complete the intervention. Interviews will be conducted by members of the study team by videoconferencing or phone. Interviews will be audio recorded with consent and transcribed verbatim. Transcripts will be offered to the participant to check for accuracy.

### Statistical methods

#### Sample size

Fifteen clinician participants will be recruited for Part One to detect a 7.6-point change in participant knowledge postupskilling with 80% power and a standard deviation of 4.3 points, accounting for 20% attrition. This sample size is informed by a previous study that utilized a similar questionnaire (Johnston *et al.*, 2013). For Part Two, as this is a feasibility trial to inform a future definitive trial, a formal sample size calculation is not appropriate. However, Browne et al. (Browne, 1995) recommend a minimum of 30 participants per arm to estimate a parameter for any future sample size calculation. Therefore, allowing for 20% attrition rate, a total of 76 participants will be recruited.

#### Quantitative data analysis

Quantitative data will be analysed using SPSS statistics package.

##### Part one

Quantitative data will be first summarized using descriptive statistics. Likert scales will be analysed as ordinal scales, 5-point scales will have values from -2 to +2 assigned. Change data will be analysed over all timepoints using ANOVA, followed by t-tests to determine where significant change occurred. Post-hoc type I error control measures will be employed. Proportions of participants meeting the defined levels of competency for the practical skills assessment will be calculated.

##### Part two

Data will be analysed in accordance with CONSORT extension for randomized pilot and feasibility trials guidelines. Intention-to-treat analysis will be used. Feasibility outcomes will be described using proportions and corresponding 95% confidence intervals (CI), or for continuous variables means, standard deviations, and ranges. The proportion of missing data will be summarized for each clinical outcome at each time point. Where possible, reasons for missing data will be recorded. Descriptive statistics will summarize clinical outcomes and effect sizes estimated. Completion rates, missing data, variances, difference, and 95% CIs pre- and post-intervention as well as between-group differences will be calculated. Change data for field walking tests will be presented as percentage changes. The proportion of participants who meet the minimum clinically important differences for each test will be calculated. For all other clinical outcomes, change data will be presented as absolute changes.

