#### Randomization, allocation, and blinding procedures

Patient participants will be randomized 1:1 to either receive the intervention or usual care. Randomization will be conducted within the randomization module of REDCap and be performed by an unblinded member of the research team. Randomization will be stratified by exercise capacity (6-minute walk distance (6MWD) ≥350m or <350m, ISWT ≥250m or <250m), and level of breathlessness with activity (modified Medical Research Council dyspnoea scale (mMRC) ≥3 or <3).

For Visit 1, clinical outcome measures will be completed by PP physiotherapists or AEPs. Randomization will occur after completion of Visit 1 data collection. The study coordinator will remain blinded to group allocation throughout the trial and will perform assessments at Visit 2. Due to the nature of the intervention, both clinician and patient participants will not be blinded to group allocation. Data will be analysed without knowledge of group allocation.

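### Clinical results in Part Two are set on change and percentage-change scales, with no baseline- or strata-adjusted estimate named for the between-group differences

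*Protocol article*

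**What the plan says.** The Part Two paragraph under Quantitative data analysis sets the scale of the clinical results. For the 6-minute walk test (6MWT) and incremental shuttle walk test (ISWT), "Change data for field walking tests will be presented as percentage changes". For the remainder, "For all other clinical outcomes, change data will be presented as absolute changes".

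The same paragraph states that "Descriptive statistics will summarize clinical outcomes and effect sizes estimated" and that variances, "difference, and 95% CIs pre- and post-intervention as well as between-group differences will be calculated". No model and no covariate is named, and the paragraph does not say that the comparison is unadjusted.

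The section on randomization says "Randomization will be stratified by exercise capacity", with separate cut-points for the two walking tests, and adds a second factor, "level of breathlessness with activity (modified Medical Research Council dyspnoea scale (mMRC) ≥3 or <3". The Outcomes section explains why there are two tests: the 6MWT needs a 30 m track, and "If there is not adequate space, the incremental shuttle walk test (ISWT) will be performed".

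Two stated purposes rest on these results. The Objectives list the comparison with usual GP care, and data for designing a definitive trial, as secondary objectives of Part Two. The Sample size section justifies 30 per arm by the wish to estimate a parameter for a later sample size calculation.

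**The concern.** The scales that the protocol fixes are not the efficient ones. A simple change score subtracts the whole Visit 1 value, whatever the correlation between visits, whereas ANCOVA estimates how much of it to subtract. Percentage change goes further and divides by a Visit 1 value measured with error. Low walkers then tend to show large percentages through regression to the mean, the distribution is right-skewed, and the spread depends on how many low walkers are enrolled and on the mix of 6MWT and ISWT, which is decided by floor space at the practice.

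Two things are at stake. The between-group intervals would be wider than the collected data allow. And the variance handed to the definitive trial would be on the wrong scale: the standard deviation of percentage change is not the residual standard deviation that a baseline-adjusted trial uses.

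**Working it through.** **Inputs.** From the protocol: 1:1 allocation, 30 per arm, 20% attrition, total 76, and the two change scales. Not in the protocol, so assumed and shown as ranges: the Visit 1 to Visit 2 correlation r and the coefficient of variation (CV) of walking distance.

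**1. The plan's own figure.** 30/(1 − 0.20) = 37.5, rounded up to 38 per arm; 2 × 38 = 76. This reproduces, so 30 analysed per arm is used below.

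**2. Absolute change against ANCOVA.** With equal variance σ² at both visits:
- variance of change: 2σ²(1 − r)
- ANCOVA residual variance: σ²(1 − r²)
- ratio: (1 − r²)/[2(1 − r)] = (1 + r)/2

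The 95% half-width in SD units is 1.96 × √(2v/30), where v is the relevant variance with σ² = 1. At r = 0.5, change has v = 1.00 and half-width 0.506; ANCOVA has v = 0.75 and half-width 0.438. The number per arm at which change scores match ANCOVA with 30 is 30/[(1 + r)/2].

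| r | variance ratio | half-width, change | half-width, ANCOVA | interval narrower by | n per arm for change to match |
|---|---|---|---|---|---|
| 0.5 | 0.75 | 0.506 | 0.438 | 13.4% | 40.0 |
| 0.6 | 0.80 | 0.453 | 0.405 | 10.6% | 37.5 |
| 0.7 | 0.85 | 0.392 | 0.361 | 7.8% | 35.3 |
| 0.8 | 0.90 | 0.320 | 0.304 | 5.1% | 33.3 |
| 0.9 | 0.95 | 0.226 | 0.221 | 2.5% | 31.6 |

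The formula is a large-sample one. Simulating the proposed model at 60 analysed, with strata unrelated to the outcome, gave variance ratios of about 0.82, 0.91 and 0.97 at r = 0.6, 0.8 and 0.9, so the gains are slightly smaller in practice.

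**3. Percentage change, additive effect.** Simulation with 30 per arm and 3,000 runs, normal data truncated at low values, and a constant additive effect of 10% of the mean (CV 0.25) or 16% (CV 0.40). The entries are the share of runs with |t| > 2.

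| CV | r | percentage change | absolute change | ANCOVA |
|---|---|---|---|---|
| 0.25 | 0.6 | 0.33 | 0.40 | 0.48 |
| 0.25 | 0.8 | 0.59 | 0.67 | 0.71 |
| 0.25 | 0.9 | 0.87 | 0.93 | 0.93 |
| 0.40 | 0.6 | 0.26 | 0.41 | 0.48 |
| 0.40 | 0.8 | 0.45 | 0.68 | 0.71 |
| 0.40 | 0.9 | 0.74 | 0.93 | 0.94 |

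These shares compare precision between scales. They are not power claims for this trial.

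**4. Percentage change, proportional effect.** This is the case that favours percentage change. Assumptions: half 6MWT and half ISWT, means 380 m and 280 m, CV 25% and 45%, true effect 0.10 on the log scale, 60 analysed. Effect divided by standard error, percentage change against ANCOVA of log distance:
- r = 0.6: 1.183 against 1.333; squared ratio 1.27
- r = 0.7: 1.385 against 1.491; squared ratio 1.16
- r = 0.8: 1.712 against 1.787; squared ratio 1.09

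The adjusted log analysis is thus worth about 27%, 16% and 9% more participants. A repeat simulation gave about 30%, 22% and 12%, and 5% at r = 0.9. The loss shrinks but stays in the same direction.

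**5. The planning parameter.** Sample size is proportional to variance. A definitive trial analysed by ANCOVA but sized on the variance of absolute change would be too large by a factor of 2/(1 + r): 1.33 at r = 0.5, 1.25 at r = 0.6, 1.05 at r = 0.9. For absolute change this can be corrected if r is reported. The standard deviation of a percentage change has no such simple conversion.

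**The case against.** The strongest reply is that the text describes reporting. Change data are to be presented on these scales, in a paragraph about descriptive statistics, and nothing there rules out an adjusted between-group estimate. Covariates and the use of strata are commonly left to an analysis plan or full protocol, which is not shown. This stands. A reader might infer that the comparison is unadjusted by decision, or that the strata are discarded; the document supports neither, because it is silent on both. A reader might also infer that Visit 1 values are ignored. They are not: change scores use them by subtraction or division. What does not fall to this reply is the scale itself, which the protocol fixes beside its promise of effect sizes and between-group intervals.

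It might also be inferred that chance baseline imbalance passes undiminished into the estimates. Stratification on Visit 1 walking distance limits that. In a simulation with 76 participants, a cut at the median and balanced allocation within strata, the standard deviation of the between-arm baseline difference fell from 0.23 to 0.14 SD. The quality-of-life and health-status scores are less protected.

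Percentage change also has a plausible purpose: metres on the 6MWT and the ISWT cannot be pooled, and a relative scale can. The protocol gives no reason, but the fix can keep a relative scale.

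Finally, the article says that the study is not powered for clinical outcomes, and the primary outcome is adherence. No decision rule depends on these intervals. That limits the weight of the point without removing it, since informing the definitive trial is a stated objective.

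**Conclusion.** The point holds as a minor to moderate improvement to secondary outcomes. The protocol sets absolute and percentage change as the scales for the clinical results and names no adjusted estimate for the between-group differences.

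Against absolute change, ANCOVA would narrow the interval by about 13% at r = 0.5, falling to 2.5% at r = 0.9, assuming equal variances at both visits and 30 analysed per arm. At high r the gain is small. Percentage change was the least precise scale in every scenario simulated, by a margin that depends on the assumed r, CV and form of the effect. None of these quantities is in the documents, so the direction is firmer than any single figure.

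It would go too far to say that the trial ignores baseline, that it has chosen an unadjusted analysis, or that its main conclusion is at risk. Adherence is unaffected, and 76 comes from a rule of thumb that this point does not touch.

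**What to change.** In the Part Two analysis text, state that each between-group difference and its 95% confidence interval will be estimated by ANCOVA of the Visit 2 value on arm, Visit 1 value and the stratification factors (exercise capacity and mMRC).

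For the walking tests, use log distance with log Visit 1 distance and test type as covariates, or analyse within each test. The back-transformed arm effect is a percentage difference, so a common relative scale for 6MWT and ISWT is kept.

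Report the residual standard deviation from each model for planning the definitive trial. Keep percentage changes, absolute changes and the proportions reaching the minimum clinically important difference as description.

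The cost is a sentence or two of wording, a few degrees of freedom and slightly more analysis work. The Visit 1 values and strata are already collected, and SPSS, the planned package, can fit the models.
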